### Adherence and Concomitant Care

In addition to scheduled clinical observations on day 1, day 3, and 48 hours after the last dose, medication adherence will be monitored throughout the study. Participants will be instructed to record daily drug intake via a medication record card, and checks will be performed at each visit to verify compliance. Any discrepancies or missed doses will be documented in the case report form. During the study period, participants will not be permitted to use any other Chinese herbal medicines for the treatment of influenza. If participants develop symptoms such as high fever, headache, or sore throat, antipyretic and analgesic medications may be used concomitantly. These medications will be provided by the study sponsor.

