#### Primary Outcome

The primary outcome is time to clinical alleviation, defined as the interval from the first dose to sustained clinical improvement, namely body temperature returning to normal, defined as an axillary temperature of ≤37 °C, and all remaining influenza symptom scores being 0 (absent) or 1 (mild) for at least 24 hours.

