#### Secondary Outcomes

The secondary outcomes are as follows:

Time to antipyretic onset: the interval from the first dose to the first documented decrease in axillary body temperature of at least 0.5 °C from baseline.Time to defervescence: time from the patient’s first dose until body temperature decreases to ≤37 °C and remains without recurrence for at least 24 hours.Changes in viral load in nasopharyngeal secretions: nasopharyngeal specimens will be collected at 2 predefined time points, day 0 (baseline) and day 5 (posttreatment), to evaluate changes in viral load over time. Viral load will be assessed using quantitative RT-PCR as a secondary virologic outcome to explore the effect of KGM on viral clearance.Individual influenza symptom scores: headache, fever or chills, myalgia, fatigue, cough, sore throat, and nasal congestion will each be scored on a 4-point ordinal scale ranging from 0 to 3, where 0 indicates absence of symptoms and 3 indicates severe symptoms.Total influenza symptom score: change from baseline and percentage change after dosing.

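### Permitted antipyretics and analgesics are ignored in the endpoint definitions: one antipyretic dose can meet time to antipyretic onset, and repeated dosing can help meet the 24-hour endpoints

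*Protocol article*

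**What the plan says.** Under Adherence and Concomitant Care, other Chinese herbal medicines for influenza are barred, but symptomatic treatment is not. The condition for use is "If participants develop symptoms such as high fever, headache, or sore throat", and then "antipyretic and analgesic medications may be used concomitantly. These medications will be provided by the study sponsor". The rule applies to both arms.

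The endpoints are fixed in the Outcomes section:

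- **Time to clinical alleviation (primary)** needs "body temperature returning to normal, defined as an axillary temperature of ≤37 °C", together with "all remaining influenza symptom scores being 0 (absent) or 1 (mild) for at least 24 hours".
- **Time to antipyretic onset** is "the interval from the first dose to the first documented decrease in axillary body temperature of at least 0.5 °C from baseline".
- **Time to defervescence** is "time from the patient’s first dose until body temperature decreases to ≤37 °C and remains without recurrence for at least 24 hours".
- **Individual symptom scores**: "headache, fever or chills, myalgia, fatigue, cough, sore throat, and nasal congestion will each be scored on a 4-point ordinal scale".

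No definition refers to antipyretic or analgesic use. Statistical Methods covers tests, analysis sets and missing data without mentioning it. The limitations paragraph of the Discussion raises short follow-up, the lack of a placebo and the open-label design, but not this.

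**The concern.** The co-medication is triggered by, and acts on, the same signs that the endpoints measure. Exposure may well be common. The TCM syndrome required at entry needs at least two major symptoms, and the two listed are fever and sore throat. Sore throat is a named reason for taking the medication, and so is fever when it is high.

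Two things are at stake. First, fever reduction is a benefit the article claims for KGM, and the endpoint meant to show how quickly it begins can be met by a different drug. Second, in a noninferiority trial anything that makes a slower arm look closer to the comparator works toward the conclusion the trial hopes to reach. Participants and treating physicians know the allocation, so use could differ between arms.

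**Working it through.** **Definitions side by side**

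| Endpoint | Must it last? | Other conditions | Condition on co-medication | Can one antipyretic dose meet it? |
|---|---|---|---|---|
| Antipyretic onset | No | None | None | Yes |
| Defervescence | 24 h | None | None | Unlikely; repeated dosing can |
| Alleviation (primary) | 24 h | All remaining symptoms at 0 or 1 | None | Not by itself; repeated dosing can contribute |

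For the primary outcome, cough, nasal congestion and fatigue must also score 0 or 1. These are not among the stated reasons for the co-medication. Headache and sore throat are stated reasons, and myalgia is another scored symptom that an analgesic can be expected to relieve.

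**Is there a figure to reproduce?** The document gives none for co-medication. The only related figures are in Sample Size. The attrition step reproduces: 78 / 0.85 = 91.8, so 92 per group and 184 in total. The 78 itself does not, because neither an SD nor a numerical KGM assumption is stated.

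**Can direction or size be derived?** The following is an illustration only, using a normal approximation to a difference in mean hours.

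- Implied SD, if 78 per group came from a 10 h margin, one-sided 0.025, 80% power and a true difference of 0: 10 × √(78/2) / (1.960 + 0.842) = 22.3 h.
- Standard error: 22.3 × √(2/78) = 3.57 h.
- Chance of declaring noninferiority at apparent difference d: Φ((10 − d)/3.57 − 1.96).

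Suppose KGM is truly 10 h slower, exactly at the margin, so that the nominal error is 2.5%. Use rates and hours gained per user are assumed; d = 10 − (KGM use − oseltamivir use) × hours gained.

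| Assumed use, KGM vs oseltamivir | Hours gained per user | d | Chance of noninferiority |
|---|---|---|---|
| 30% vs 30% | 10 or 20 | 10 | 2.5% |
| 50% vs 30% | 10 | 8 | 8.1% |
| 50% vs 30% | 20 | 6 | 20.1% |
| 30% vs 50% | 10 | 12 | 0.6% |
| 30% vs 50% | 20 | 14 | 0.1% |

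Equal additive use leaves the difference unchanged. Heavier use in the KGM arm inflates the error, and heavier use in the oseltamivir arm deflates it. If planning instead assumed KGM 10 h faster, the implied SD doubles to 44.6 h and the standard error to 7.14 h. The 8.1% and 20.1% then become 4.7% and 8.1%. The error thus runs from well below to well above nominal, depending on inputs the document does not contain.

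**The case against.** The strongest defence is that the passages do not contradict each other. Counting outcomes regardless of permitted symptomatic care is a recognised treatment-policy choice, and the handling of concomitant medication is commonly left to the statistical analysis plan, which is not shown. This stands for the primary outcome and defervescence: there is no ground for calling those definitions wrong or for replacing them. It does not rescue antipyretic onset. That event is defined in the article itself and, followed as written, credits a co-medication response to study drug.

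A reader might infer more than the document supports:

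- *That the comparison is biased toward no difference.* Convergence is plausible where co-medication relief replaces study-drug relief, but it is an inference. An equal additive shift changes nothing in hours, and heavier use in the oseltamivir arm works against KGM.
- *That relief of pain or fever by one dose counts as primary success.* It does not: temperature, all remaining scores and 24 hours must be satisfied together.
- *That a true deficit shrinks in proportion to the share of co-medicated events*, so that 15 h becomes 15 × (1 − 0.5) = 7.5 h, inside the 10 h margin. This assumes such events carry no arm difference at all. It also compares a point estimate with the margin, whereas noninferiority depends on the confidence limit. Even on that model and the 22.3 h SD, noninferiority would be declared 10.4% of the time at a 50% share and 1.8% at 30%.
- *That supply by the sponsor is a flaw.* It is not one in itself.

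**Conclusion.** The point holds in a limited form. Time to antipyretic onset is badly defined: where an antipyretic is taken before the first 0.5 °C fall, the event cannot be attributed to either study drug. This follows from the wording alone and needs no assumption about rates of use, although the number of participants affected is unknown.

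For alleviation and defervescence the weakness is smaller. The 24-hour condition blunts the effect of a single dose, and the other symptom scores protect alleviation further, but a window held by repeated dosing still counts. A KGM deficit could be masked in this way. Direction and size are not determinable, and the figures above rest on an assumed SD, assumed use and assumed hours gained. This is worth correcting, but it is not grounds for rejecting the primary endpoint.

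**What to change.** Leave permitted use as it is and change only the derivation and reporting.

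1. **Antipyretic onset.** Count as an event only a fall documented before any antipyretic dose. Treat participants who take an antipyretic first as not having reached the event during follow-up. Do not censor them at the dose: those still febrile are the ones likely to dose, so such censoring would be informative. Report the current definition as a sensitivity analysis.
2. **Alleviation and defervescence.** Keep the current definitions. Add a prespecified supplementary analysis that accepts the 24-hour window only if it is free of antipyretic and analgesic doses, with any washout set by the sponsor's clinicians.
3. **Data.** Record dose times on the existing medication card where still possible, and fall back on daily records otherwise. Report use by arm.

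The cost is a card or case report form field, revised wording for one secondary endpoint and one extra analysis. Onset events will be later or fewer, and the decision to take an antipyretic, made open label, becomes part of that endpoint. Recruitment began in September 2025 and was due to finish in June 2026, so dose times will be incomplete for participants already enrolled. The change should be made promptly and before the outcome data are analysed.

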### Outcomes

#### Overview

The assessment schedule is summarized in Table 1.

**Table 1 table1:** Assessment schedule of the trial.

Assessments			Baseline (day 0)		Day 3		Day 5
**Eligibility and enrollment**							
	Inclusion criteria	✓					
	Exclusion criteria	✓					
	Informed consent	✓					
	Baseline assessment	✓					
	Randomization and allocation	✓					
**Primary outcome measurement**							
	Time to symptom relief	✓		✓		✓	
**Secondary outcome measurements**							
	Time to onset of antipyretic effect	✓		✓		✓	
	Duration of antipyretic effect	✓		✓		✓	
	Changes in viral load in nasopharyngeal secretions	✓				✓	
	Individual influenza symptom score	✓		✓		✓	
	Total influenza symptom score	✓		✓		✓	
	Changes in the traditional Chinese medicine syndrome score compared with baseline	✓				✓	
**Safety assessments**							
	Blood routine tests	✓				✓	
	Urine routine tests	✓				✓	
	Liver and renal function assessments	✓				✓	
	Electrocardiograms and chest radiography	✓				✓	
Adverse events			✓		✓		✓

#### Primary Outcome

The primary outcome is time to clinical alleviation, defined as the interval from the first dose to sustained clinical improvement, namely body temperature returning to normal, defined as an axillary temperature of ≤37 °C, and all remaining influenza symptom scores being 0 (absent) or 1 (mild) for at least 24 hours.

#### Secondary Outcomes

The secondary outcomes are as follows:

Time to antipyretic onset: the interval from the first dose to the first documented decrease in axillary body temperature of at least 0.5 °C from baseline.Time to defervescence: time from the patient’s first dose until body temperature decreases to ≤37 °C and remains without recurrence for at least 24 hours.Changes in viral load in nasopharyngeal secretions: nasopharyngeal specimens will be collected at 2 predefined time points, day 0 (baseline) and day 5 (posttreatment), to evaluate changes in viral load over time. Viral load will be assessed using quantitative RT-PCR as a secondary virologic outcome to explore the effect of KGM on viral clearance.Individual influenza symptom scores: headache, fever or chills, myalgia, fatigue, cough, sore throat, and nasal congestion will each be scored on a 4-point ordinal scale ranging from 0 to 3, where 0 indicates absence of symptoms and 3 indicates severe symptoms.Total influenza symptom score: change from baseline and percentage change after dosing.

### Safety Assessments

No SAEs related to KGM have been reported, and systematic safety monitoring is planned. The parameters will include vital signs, complete blood count, urinalysis, hepatic and renal function tests, 12-lead electrocardiography, chest radiography, and AE surveillance.

### AE Management

All AEs will be recorded in the case report form, investigated thoroughly, and followed up until resolution or stabilization. Severity will be graded as mild, moderate, or severe. Follow-up modalities (inpatient care, outpatient visits, home visits, and telephone contacts) will be tailored to severity and clinical need. All SAEs will be reported to the ethics committee within 24 hours. Withdrawal criteria will include the following: (1) occurrence of an SAE related to the study intervention, (2) poor compliance with the study protocol, (3) participant request to withdraw, or (4) other medical conditions deemed inappropriate for continuation by the investigators.

### Statistical Methods

Study data will be entered into the electronic database independently by 2 trained research staff members, and discrepancies will be resolved by cross-checking to ensure accuracy. All data will be stored in a password-protected, access-restricted electronic database, with access limited to authorized study personnel.

Data management and analysis will be performed using SAS (version 9.4; SAS Institute) according to a prespecified statistical analysis plan. Statistical significance will be defined as a 2-sided *P* value of <.05, and 95% CIs will be reported.

Continuous variables will be summarized as mean (SD) for normally distributed data or median (IQR) for nonnormally distributed data. Categorical variables will be presented as frequencies and percentages. Normality will be assessed using the Shapiro-Wilk test, and the equality of variances will be examined using the Levene test. Between-group comparisons of continuous end point will be performed using an independent-sample 2-tailed *t* test (normal data) or the Mann-Whitney *U* test (nonnormal data). Categorical outcomes will be compared with the chi-square test or Fisher exact test, as appropriate. McNemar test will be performed to evaluate paired proportions when preintervention and postintervention data are available. All analyses will be conducted on both the full-analysis and per-protocol populations. For the primary outcome, missing data will be handled using multiple imputation, following current best practices, to reduce potential bias and improve the robustness of the findings. In addition, a sensitivity analysis will be performed using complete-case (listwise deletion) analysis to examine the consistency of the results under different missing-data assumptions.

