Traditional Chinese medicine (TCM), with centuries of clinical antiviral experience, offers alternative strategies. The evidence suggests that combining TCM with oseltamivir shortens fever duration, hastens symptom resolution, and reduces the length of stay [9]. An open-label trial further revealed that TCM monotherapy for H1N1 influenza achieved a fever reduction equivalent to that of oseltamivir [10]. Kanggan mixture (KGM), a TCM widely used in clinical practice, is effective at dispersing wind heat, clearing heat, and resolving toxins. Over the past 2 decades, it has been widely used for the treatment of influenza in clinical practice, demonstrating consistent benefits for fever reduction and symptom improvement. KGM was originally an empirical prescription by [name], a famous Chinese medicine practitioner. It became an in-hospital preparation at Jiangsu Province Hospital of Chinese Medicine in 1998 and was approved by the Jiangsu Food and Drug Administration in 2006 (approval number Z20060004). The formula is composed of 12 botanical drugs, including honeysuckle, forsythia, mint, Platycodon, bitter almond, *Bistortae isatis root, Dryopteris crassirhizoma*, *Cimicifuga*, *Chizonepeta*, *Ligusticum chuanxiong*, and licorice. A previous study demonstrated that compared with the control, KGM had an efficacy rate of 96.67% for acute viral upper respiratory infection and reduced the time to defervescence [11].

However, high-level evidence of the efficacy of KGM in the treatment of influenza is lacking, and its safety profile requires systematic evaluation. Therefore, we designed this prospective, open-label, randomized, parallel-controlled, noninferiority trial to compare the efficacy and safety of KGM and oseltamivir in adults with influenza.

Therefore, we designed this prospective, multicenter, open-label, randomized, parallel-group, noninferiority trial to compare the efficacy and safety of KGM with those of oseltamivir in adults with influenza. We hypothesize that KGM is noninferior to oseltamivir in shortening the time to clinical alleviation and may improve influenza-related clinical outcomes with an acceptable safety profile.

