### Sample Size

The sample size was determined based on the primary end point, namely the median time to the alleviation of influenza symptoms. Published studies have reported that the median time to symptom alleviation with oseltamivir is approximately 80 hours [14,15]. The assumption for KGM was informed by preliminary clinical evidence and prior clinical experience [11]. A noninferiority margin of 10 hours was prespecified with consideration of its clinical relevance and the feasibility of the trial. Under the assumptions of a 1:1 allocation ratio, a 2-sided significance level of .05, and 80% power, 78 evaluable participants were required per group. After accounting for an anticipated attrition rate of 15%, the target enrollment was set at 92 participants in each group, resulting in a total sample size of 184 participants.

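### The stated analysis names only tests of no difference and ties no confidence limit to the 10-hour margin, so it does not test the trial's noninferiority hypothesis

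*Protocol article*

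**What the plan says.** The hypothesis in the Introduction is plain: "We hypothesize that KGM is noninferior to oseltamivir in shortening the time to clinical alleviation". The Sample Size section works from the median time to alleviation, takes it that "the median time to symptom alleviation with oseltamivir is approximately 80 hours", and sets the margin: "A noninferiority margin of 10 hours was prespecified with consideration of its clinical relevance and the feasibility of the trial". It continues: "Under the assumptions of a 1:1 allocation ratio, a 2-sided significance level of .05, and 80% power, 78 evaluable participants were required per group".

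The Statistical Methods section then gives the analysis. "Between-group comparisons of continuous end point will be performed using an independent-sample 2-tailed" *t* test if the data are normal, or by the Mann-Whitney *U* test if they are not, with normality judged by Shapiro-Wilk. Chi-square, Fisher exact and McNemar tests cover categorical outcomes. The threshold is a 2-sided P value below .05, and 95% CIs will be reported. On populations it says "All analyses will be conducted on both the full-analysis and per-protocol populations". For the primary outcome it specifies multiple imputation and a complete-case sensitivity analysis, but no separate test. Neither noninferiority nor the margin appears in that section. A prespecified statistical analysis plan is mentioned; it is not available here.

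**The concern.** Every test named in Statistical Methods has no difference as its null hypothesis. A noninferiority trial needs the opposite: a null that KGM is slower by at least the margin, rejected only when the data exclude a deficit that large. P>=.05 from a difference test does not exclude a 10-hour deficit. P<.05 in favor of oseltamivir does not show that the deficit exceeds 10 hours.

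The quantity to set against the margin is not fixed either. The margin belongs to a median. The *t* test compares means, and a Mann-Whitney P value gives no estimate in hours. Which of the two is used depends on a normality test run on the trial data. The headline conclusion, that KGM is or is not an alternative to oseltamivir, rests on this comparison.

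**Working it through.** **Inputs from the protocol article (Sample Size).** Margin 10 h; oseltamivir median about 80 h; 2-sided .05 (one-sided .025 for noninferiority); 80% power; 78 evaluable per group; 15% attrition. No SD, hazard ratio or KGM value is given.

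**1. The plan's own figures.** Enrollment reproduces: 78 / (1 − 0.15) = 91.8, so 92 per group and 184 in total. The 78 cannot be reproduced without an SD or a KGM value. Treating the outcome as a difference in means, n per group = 2·SD²·(1.960 + 0.842)² / (10 − true difference)². Solving for the SD that gives 78:
- True difference 0: SD = 10·√(78/2) / 2.802 = 22.3 h.
- KGM 5 h faster: 15·√39 / 2.802 = 33.4 h.
- KGM 10 h faster: 20·√39 / 2.802 = 44.6 h.

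**2. A nonsignificant P compared with a margin rule (means, normal approximation).** SE = SD·√(2/78). If KGM is truly 10 h slower, P(nonsignificant) = Φ(1.96 − 10/SE) − Φ(−1.96 − 10/SE). If the arms are equal, the power of the rule (upper 95% limit below 10 h) is Φ(10/SE − 1.96). SDs above 22.3 are assumptions.

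| SD (h) | SE (h) | Nonsignificant when truly 10 h slower | Power of margin rule when equal |
|---|---|---|---|
| 22.3 | 3.57 | 20.0% | 80.0% |
| 30 | 4.80 | 45.2% | 54.8% |
| 40 | 6.41 | 65.5% | 34.5% |
| 50 | 8.01 | 76.1% | 23.9% |

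At a true 10-h deficit the margin rule wrongly declares noninferiority 2.5% of the time, whatever the SD.

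**3. Mann-Whitney (simulation).** 4000 trials per scenario, 78 per arm, oseltamivir median 80 h, Weibull shapes 1 / 1.5 / 2 (assumed). Proportion with P>=.05:
- KGM median 90 h: about 90% / 85% / 76%.
- KGM median 100 h (twice the margin): about 77% / 57% / 35%. Repeat runs differ by two to three points at the largest shape.
- KGM median 100 h, with onsets after 96 h ranked as unresolved: about 83% / 67% / 49%. The 96 h is 5 days (120 h) less the 24 h of sustained relief that the primary outcome requires. This cut-off is an assumption, because the Adherence section also lists an observation 48 h after the last dose.

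**4. Power of the corrected rule on the median difference.** With both medians at 80 h and full follow-up, the Weibull density at the median is f = shape·ln2 / (2·80), and the SE of the difference in medians is √2 / (2·f·√78).
- Shape 1: f = 0.00433, SE = 18.5 h, power = Φ(10/18.5 − 1.96) = 8%.
- Shape 1.5: f = 0.00650, SE = 12.3 h, power = 13%.
- Shape 2: f = 0.00866, SE = 9.2 h, power = 19%.

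Simulation with bootstrap intervals gives the same order, about 7% to 20%.

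**The case against.** The best defense has four parts.

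First, the article does promise 95% CIs, and it promises every analysis in both the full-analysis and per-protocol sets. A 2-sided 95% CI is the usual vehicle for a noninferiority decision and matches the 2-sided .05 used for sizing. This stands as far as it goes: the tool is there. But the article does not say what the CI estimates or that any limit will be held against 10 hours.

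Second, the sentence on the *t* test and Mann-Whitney is generic to continuous end points, and a separate analysis plan may hold the noninferiority rule. That plan cannot be excluded. Yet the section is not silent: it names tests and a threshold, treats the primary outcome specifically for missing data, and offers no other test for it. The conflict with the Introduction and Sample Size sections is in the published text itself.

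Third, a reader might infer that the sponsor intends to treat a nonsignificant P value as noninferiority. The documents do not support this, because no sentence says how noninferiority will be declared. The error rates above show what such a misreading would cost, not what the plan has adopted. For the same reason one cannot say that the trial is unable to support its claim. What to conclude if the two analysis sets disagree is detail that an article may leave to the analysis plan, and it is not counted here.

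Fourth, the obvious remedy is not free: the low power in step 4 is real and has to be disclosed with it.

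**Conclusion.** The point holds as a mismatch inside the protocol article. The hypothesis and margin are for noninferiority, while the named tests and threshold are for a difference, and the promised CIs are not linked to the margin. If a nonsignificant Mann-Whitney result were misread as noninferiority, a drug 20 hours slower would pass in roughly a third to three quarters of trials (35% to 77%), given 78 per arm and assumed Weibull shapes of 2 down to 1.

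The article shows only that the rule is not stated where the analysis is described, not that no rule exists elsewhere. The sample size is a linked weakness. With equal arms, 80% power on a mean difference needs an SD near 22 h. On the median difference, power is about 7% to 20% under the assumed shapes. A KGM advantage built into the sizing would change these figures, but the article gives no value for it. The point should be settled before outcome data are examined; recruitment is expected to end in June 2026 and publication is anticipated by December 2026.

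**What to change.** For the primary outcome, replace the normality-switched difference test with one prespecified effect measure in hours that matches the margin: the difference in median time to alleviation, KGM minus oseltamivir. Estimate it by a method that handles patients not alleviated by the end of follow-up, such as Kaplan-Meier medians with a bootstrap interval. Declare noninferiority only if the upper limit of the 2-sided 95% CI is below +10 hours. Report this in both the full-analysis and per-protocol sets. State that P>=.05 from a difference test is not evidence of noninferiority. If the analysis plan already contains such a rule, bring the published text into line with it.

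Recheck the 80% power for this rule and restate it with the assumed KGM median and the spread or distribution used.

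The direct cost is wording and one programmed analysis, with no effect on patients. The real cost is that 78 evaluable per arm may prove far too few for a 10-hour margin on a median, and the sponsor should say so before the results are known. Incomplete follow-up makes this harder, because with a day-5 cut-off the upper limit for the median may often not be estimable.

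### The between-arm tests stated for the 0–3 symptom scores do not fit an ordinal scale: read literally they lead to chi-square or Fisher, and under either reading the baseline score goes unused

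*Protocol article*

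**What the plan says.** Secondary Outcomes lists seven symptoms (cough, fatigue, sore throat, nasal congestion, myalgia, headache, and fever or chills). Of these it says that they "will each be scored on a 4-point ordinal scale ranging from 0 to 3". Table 1 schedules these scores at baseline, day 3 and day 5.

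Statistical Methods sorts outcomes by type:

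- Continuous: "Between-group comparisons of continuous end point will be performed using an independent-sample 2-tailed" t test, or a Mann-Whitney U test when the data are not normal. Normality is judged by the Shapiro-Wilk test.
- Categorical: "Categorical outcomes will be compared with the chi-square test or Fisher exact test, as appropriate".

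There is no ordinal class. None of the listed between-arm tests uses the baseline value. The section also says that analysis will run "according to a prespecified statistical analysis plan", which is not shown.

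**The concern.** The article calls the scores ordinal and then states rules that have no place for ordinal data. The rule that contains a rank test is reserved for continuous end points, so on plain wording a four-level score goes to chi-square or Fisher. On a 2×4 table these tests treat 0, 1, 2 and 3 as unordered labels. They lose power against a consistent shift, and they can be significant when neither arm is better.

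Each score is also measured at baseline, and every stated between-arm test ignores that measurement.

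Symptom scores are among the secondary outcomes named in the abstract, and the introduction hypothesises that KGM may improve influenza-related outcomes. With seven symptoms and two post-baseline visits there are 7 × 2 = 14 comparisons. It should be settled before the data are seen whether a rank test or an unordered test is used for them.

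**Working it through.** **1. Numbers per arm.** Sample Size gives 78 evaluable per group, 15% attrition and "a 2-sided significance level of .05, and 80% power". Check: 78 / (1 − 0.15) = 91.8, so 92 per group and 184 in total, as stated. The article prints no distribution or effect size for the symptom scores, so the power figures below rest on assumptions. All use two-sided 0.05.

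**2. Chi-square ignores order.** Take an example with 78 per arm and scores 0/1/2/3 of 40/20/12/6 against 25/25/18/10. The column totals are 65, 45, 30 and 16, so the expected counts per arm are 32.5, 22.5, 15 and 8.

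χ² = 2 × (7.5²/32.5 + 2.5²/22.5 + 3²/15 + 2²/8) = 2 × (1.731 + 0.278 + 0.600 + 0.500) = 6.22 on 3 df, p = 0.102.

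Shuffling the columns leaves this sum unchanged. Mann-Whitney gives p = 0.016 in the true order and p = 0.665 after one shuffle (columns taken in the order 2, 0, 3, 1), so it does use the order.

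The reverse can also happen. For 30/9/9/30 against 15/24/24/15, the expected counts are 22.5, 16.5, 16.5 and 22.5. Then χ² = 2 × (2 × 7.5²/22.5 + 2 × 7.5²/16.5) = 2 × (5.000 + 6.818) = 23.64, p = 0.00003. Mann-Whitney gives p = 1.0: highly significant, with neither arm better.

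**3. Power if the literal rule is followed.** The second arm is obtained by multiplying each cumulative odds by the odds ratio (OR). For the assumed day 3 control of 20/40/30/10%, the cumulative proportions are 0.2, 0.6 and 0.9, with odds 0.25, 1.5 and 9. Doubling gives 0.5, 3 and 18, hence 0.333, 0.750 and 0.947, which is 33.3/41.7/19.7/5.3%. The assumed day 5 control is 40/40/15/5%. Simulated power, 78 per arm, 3000 trials per setting:

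| Setting | Chi-square, 4 categories | Mann-Whitney | Gap (points) |
|---|---|---|---|
| Day 3, OR 1.8 | 34.1% | 50.6% | 16.5 |
| Day 3, OR 2.0 | 46.9% | 65.7% | 18.8 |
| Day 3, OR 2.3 | 64.3% | 80.3% | 16.0 |
| Day 5, OR 1.8 | 33.4% | 48.9% | 15.5 |
| Day 5, OR 2.0 | 45.1% | 62.3% | 17.2 |
| Day 5, OR 2.3 | 62.0% | 77.9% | 15.9 |

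A second run with other control distributions (35/35/20/10, 50/30/15/5 and 25% in each category) gave, at OR 2, 42–49% for chi-square and 59–67% for Mann-Whitney. At OR 2.5 it gave 66–76% and 83–88%. Type I error was near 5% for both tests.

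**4. If the scores are treated as numbers.** Shapiro-Wilk on simulated four-level scores, n = 78, rejected normality in 100% of runs for every distribution tried. The written rule would then select Mann-Whitney, and the gap in step 3 disappears.

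**5. Baseline adjustment.** In a further simulation with a baseline score (78 per arm, OR 2, assumed distributions), power was about 31–45% for chi-square, 45–62% for Mann-Whitney and 58–63% for a proportional-odds model with the baseline score. Type I error was near 5%. Comparing the ends of the ranges, chi-square trails Mann-Whitney by 45 − 31 = 14 points at the low end and 62 − 45 = 17 at the high end. The adjusted model is ahead of Mann-Whitney by 58 − 45 = 13 points at the low end and 63 − 62 = 1 at the high end. This is only indicative, because range ends need not come from the same setting. The gain depends on how strongly baseline predicts the later score, which the article does not report. If baseline predicts nothing, there is essentially no gain.

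**The case against.** The strongest reply is that the article never assigns these scores to chi-square or Fisher. They are numeric, they feed a total score analysed as change and percentage change, and a reader could fairly place them in the continuous branch, where Mann-Whitney would follow (step 4). The categorical rule has other natural uses, such as adverse event occurrence, so it does not need the symptom scores to have a purpose. The separate analysis plan may settle the matter. All of this stands. It makes the 14–19 point loss conditional and rules out saying that the trial will discard the ordering.

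It does not remove the point. The article commits to tests by outcome type, labels this outcome ordinal, and limits its rank test to continuous end points, so its own wording leads to the worse test. The benign reading still leaves baseline unused.

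A reader might also infer that the pre/post test is meant as evidence of KGM efficacy on symptoms, since the section adds that "McNemar test will be performed to evaluate paired proportions when preintervention and postintervention data are available". The text does not support that. It names no outcome for this test, proposes no cut of the symptom scores, and lists the between-group tests separately. Safety tests done at baseline and day 5 are an equally plausible use.

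**Conclusion.** The point holds as a mismatch between an ordinal secondary outcome and the stated test rules, not as a demonstrated wrong analysis. On the literal reading the cost is roughly 14 to 19 points of power against a rank test, at 78 per arm and a common odds ratio of 2. On the numeric reading the only cost is the forgone baseline adjustment, which ranges from almost nothing to around 13 points. Both sizes rest on assumed score distributions, a proportional-odds shift and, for the second, an assumed link between baseline and later scores.

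A reader might go further and infer that the noninferiority conclusion is weakened. It is not. "A noninferiority margin of 10 hours was prespecified" for time to symptom alleviation, and neither that outcome nor the sample size depends on how the individual scores are tested.

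**What to change.** In Statistical Methods, or in the analysis plan if it does not already say so, state that each individual symptom score at day 3 and day 5 is compared between arms on the full 0–3 scale. Use a proportional-odds model with treatment and that symptom's baseline score, and report the common odds ratio with its 95% CI. Name the Wilcoxon/Mann-Whitney test as the fallback. Reserve chi-square and Fisher for nominal or binary outcomes.

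The cost is one or two sentences and standard SAS procedures; no further data or participants are needed. The drawbacks are small: the proportional-odds assumption has to be checked, and a common odds ratio is less familiar to clinical readers than a percentage. The wording should be fixed before the data are analysed.
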